#### Economic outcomes

The analysis of economic outcomes will also be conducted in agreement with the intention-to-treat principle. An incremental cost-utility ratio (ICUR) will be calculated by dividing the incremental costs (i.e. mean costs in the intervention group minus mean costs in the control group) by the incremental QALYs (i.e. mean QALYs in the intervention group minus mean QALYs in the control group).

Total costs from a societal perspective will be calculated using intervention costs, costs of healthcare (i.e. costs of healthcare and medication), costs for patients and their families (e.g. travelling costs and help received from family and friends), and costs within other sectors (i.e. productivity losses from paid and unpaid work). Intervention costs and costs of healthcare will be used to calculate total costs from a healthcare perspective.

Costs of healthcare and costs for patients and their families will be calculated by multiplying resource use by integral costs prices as presented in the Dutch Health Care Insurance Board (CVZ) guidelines on cost studies [42]. The friction cost method will be used to calculate the costs within other sectors [43, 44].

The time horizon will be set at three months follow-up; therefore, neither costs nor effects will be discounted. The EQ-5D utility score will be used to calculate QALYs by linking the scores to the various health states of the EQ-5D. Multiple imputation will be used when data are missing on the costs of healthcare, the costs of patients and their families, and the costs within other sectors. This also accounts for missing data on the utilities measured with the EQ-5D.

To obtain 95% confidence intervals around the costs and QALY differences, non-parametric bootstrapping with 5000 imputations will be used. A cost-utility plane will be plotted for the projection of the resulting pairs of cost and effect differences. A cost-effectiveness acceptability curve will be made to reflect the probability of Oncokompas being cost-effective given different willingness-to-pay ceilings [45]. Sensitivity analyses will be conducted focusing on uncertainty in the main cost factors.

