### Outcome assessment

Caregiver burden is the primary outcome measure used to assess the efficacy of Oncokompas among partners of patients with incurable cancer. Secondary outcome measures are general self-efficacy and health-related quality of life. In addition, outcomes on cost-utility will be measured.

Measurements will be collected at baseline (t0), two weeks after randomization (t1), and three months after the baseline measurement (t2). Measurements will be assessed through online questionnaires. An overview of the primary and secondary outcome measures is shown in Table 3.

**Table 3 Tab3:** Measurement overview

Aim		Outcome measures	Instrument
Efficacy	Primary outcome measure Secondary outcome measures	Caregiver Burden Self-efficacy	Caregiver Strain Index + (CSI+) General Self-Efficacy Scale (GSE)
Cost-utility		Health-related quality of life Medical costs Productivity costs Costs of Informal Care	EuroQol 5 Dimensions (EQ-5D-5L) iMTA Medical Consumption Questionnaire (iMCQ) iMTA Productivity Cost Questionnaire (iPCQ) iMTA Valuation of Informal Care Questionnaire (iVICQ)

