#### Medical consumption questionnaire, productivity cost questionnaire, and valuation of informal care questionnaire

To measure the costs of healthcare, the costs for patients and their families (e.g. travelling costs and help received from family and friends), and costs within other sectors (i.e. productivity losses from paid and unpaid work) in the previous three months, an adapted version of the medical consumption questionnaire (iMCQ) and productivity cost questionnaire (iPCQ) will be used. An adapted version of the valuation of informal care questionnaire (iVICQ) will be used for the valuation of informal care by monetary and non-monetary methods. All these questionnaires are developed by the Institute for Medical Technology Assessment of the Erasmus University Rotterdam (iMTA), the Netherlands [38–40].

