### Statistical analyses

All analyses will be conducted in agreement with the intention-to-treat principle. Descriptive statistics will be used to describe the sociodemographic characteristics, health-related characteristics of the partner, the health situation of the patient with cancer, and the outcome measures. Chi-square tests and independent samples t-tests will be used to analyze whether randomization resulted in a balanced distribution of sociodemographic and health-related characteristics across the study arms. Mann–Whitney U tests will be performed in case of non-normality of the data. To test whether there are differences in the outcomes across the study arms at baseline, independent samples t-tests will be used.

Linear mixed models (LMM) will be used to determine the efficacy of Oncokompas by comparing longitudinal changes between the intervention group and control group with fixed effects for study arm, time, and their two-way interaction, as well as a random intercept for individuals.

LMM will also be used to determine whether age, gender, socioeconomic status (e.g. education level and work situation), the health situation of the patient, and baseline quality of life moderate the efficacy of Oncokompas with fixed effects for study arm, time, the potential moderator, and all two-way and three-way interaction effects, as well as a random intercept for individuals.

Post-hoc analyses will be applied when significant results are found in the efficacy and moderation analyses. To measure the differences in change between the intervention group and control group at follow-up measurements, independent samples t-tests with Bonferroni correction will be used. These tests will also be used to assess whether change scores between the intervention group and control group differed significantly within each category of the significant moderator variables.

The effect sizes (ES) of the intervention will be measured by calculating the (between group) Cohen’s d. The magnitude of the ES is classified as large (≥ 0.80), moderate (0.50–0.79) or small (< 0.50) [41].

A *p* value < 0.05 will be considered significant for all analyses. All tests will be one-tailed. IBM Statistical Package for the Social Sciences (SPSS) version 26 (IBM Corp., Armonk, NY USA) will be used to perform all statistical analyses.

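### Incremental QALYs are a raw difference in arm means although EQ-5D is measured at baseline: unbiased on average, but less precise than it could be and shifted by any chance imbalance in baseline utility

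*Protocol article*

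**What the plan says.** The Economic outcomes section of the protocol article defines both halves of the ICUR. Incremental costs are "mean costs in the intervention group minus mean costs in the control group" and incremental QALYs are "mean QALYs in the intervention group minus mean QALYs in the control group". No regression and no covariate is named for either.

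Uncertainty is handled in the same section: "To obtain 95% confidence intervals around the costs and QALY differences, non-parametric bootstrapping with 5000 imputations will be used". The cost-utility plane and the acceptability curve are built from the same pairs of differences. The only sensitivity analyses planned concern costs: "Sensitivity analyses will be conducted focusing on uncertainty in the main cost factors".

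Baseline values are available. Under Outcome assessment the article states "Measurements will be collected at baseline (t0), two weeks after randomization (t1), and three months after the baseline measurement (t2"), and the abstract's Methods paragraph includes health-related quality of life among the measures taken at baseline. The Statistical analyses section compares arms at baseline ("To test whether there are differences in the outcomes across the study arms at baseline, independent samples t-tests will be used") but attaches no consequence to the result for the economic analysis. The mixed model with an arm-by-time interaction takes each arm's starting level into account, but it serves efficacy only. Baseline quality of life otherwise appears only as a possible moderator of efficacy.

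**The concern.** A QALY accrued over three months depends in part on where the partner started. If QALYs are an area under the utility curve that includes t0, baseline utility enters directly. In any case it is correlated with utility at t1 and t2. An arm that happens to start with better utility will, on expectation, show more QALYs even if the application does nothing.

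The horizon is 0.25 year and the sample was sized for the caregiver strain outcome, so incremental QALYs will be small and the ICUR denominator close to zero. A shift of a few thousandths of a QALY can then change the ratio noticeably or move the point estimate to another quadrant. The article expects the results to inform policy makers, so an avoidable source of noise in this estimate is worth removing.

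**Working it through.** **Inputs from the article.** There are 68 partners per arm at baseline (Sample size; 51/(1 - 0.25) = 68 reproduces). The horizon is three months, and visits are at baseline, two weeks and three months, taken here as 0, 2 and 13 weeks. The article gives no figure of its own for the precision of the QALY difference, so there is none to reproduce.

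**Assumptions, not in the article.**
- Utility SD of 0.10 to 0.25, equal at all visits.
- Within-person correlations t0-t1, t1-t2 and t0-t2 from 0.6, 0.55, 0.5 (low) to 0.8, 0.75, 0.7 (high).
- QALY computed by the trapezium rule over all three visits.
- As a benchmark, a true utility gain of 0.05 at both t1 and t2.

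**Step 1: weights in years.**
- t0: (2/52)/2 = 0.0192
- t1: (13/52)/2 = 0.125
- t2: (11/52)/2 = 0.1058
- Sum: 0.25

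**Step 2: slope of QALY on baseline utility**, w0 + w1·r01 + w2·r02.
- Low: 0.0192 + 0.125×0.6 + 0.1058×0.5 = 0.147
- High: 0.0192 + 0.125×0.8 + 0.1058×0.7 = 0.193

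**Step 3: shift from a one-SE baseline imbalance**, slope × SD × sqrt(2/68). The benchmark gain is 0.05 × (0.125 + 0.1058) = 0.0115 QALY.

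| Assumed SD | SE of baseline difference | Shift in incremental QALYs | Share of 0.0115 |
|---|---|---|---|
| 0.10 | 0.0171 | 0.0025-0.0033 | 22-29% |
| 0.20 | 0.0343 | 0.0050-0.0066 | 44-57% |
| 0.25 | 0.0429 | 0.0063-0.0083 | 55-72% |

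An imbalance of at least one SE in either direction occurs in about 32% of trials. It would not be flagged by the planned baseline t-test (one-tailed p about 0.16).

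**Step 4: variance removed by adjustment**, slope² / var(QALY), both in units of SD².
- var(QALY) = w0² + w1² + w2² + 2(w0·w1·r01 + w0·w2·r02 + w1·w2·r12) = 0.0466 (low) and 0.0537 (high)
- Low: 0.1471²/0.0466 = 0.46
- High: 0.1933²/0.0537 = 0.70

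The SD cancels. At SD 0.20 the SE of the QALY difference falls from 0.0074 to 0.0054 (low) or from 0.0079 to 0.0044 (high).

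**Step 5: if only t0 and t2 enter the QALY.** Each has weight 0.125. The slope is 0.125(1 + r) and the share of variance removed is (1 + r)/2: 75% at r = 0.5, 85% at 0.7 and 90% at 0.8.

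**Step 6: costs.** Adjustment removes r² of the variance, where r is the correlation between costs before randomization and during follow-up. This is 9%, 25% or 49% for assumed r of 0.3, 0.5 or 0.7.

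**The case against.** The wording about means is a parenthetical gloss in a condensed article, and a fuller plan might specify a regression. That has some force, but the plain reading is an unadjusted subtraction, and the bootstrap, plane and curve are described on that basis.

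The stronger objection concerns what the raw difference does. A reader might infer that the ICUR is biased, or that any baseline difference is simply booked as an effect of the application. The article does not support that. Allocation is randomized 1:1, so the raw difference is unbiased over repeated trials. The bootstrap resamples people together with their baseline values, so the intervals, plane and curve already carry this variation. The one-SE shift is 0.68 to 0.83 of the unadjusted SE and so lies inside the uncertainty that will be reported. What stands is narrower: the interval is wider than it needs to be, and it is centred on an estimate displaced by an imbalance that is known once the data are in.

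The size is also open to challenge. Neither the SD nor the 0.05 gain comes from the article, and the share of the benchmark gain halves when the SD is 0.10 rather than 0.20. With three visits the direct weight of baseline is only 0.0192 of 0.25 year, so most of the shift runs through assumed correlations. Adjustment does not remove instability either: at SD 0.20 the adjusted SE is still 38-47% of 0.0115.

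A reader might also infer that costs suffer equally. They do not. The questionnaires look back ("in the previous three months, an adapted version of the medical consumption questionnaire (iMCQ) and productivity cost questionnaire (iPCQ) will be used"), so a baseline measurement covers the time before randomization and is no part of the follow-up total. Only general statements indicate that costs are collected at t0, and the schedule figure is not shown.

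**Conclusion.** The point holds for QALYs as a matter of precision and of conditional bias given the observed baseline imbalance, not as systematic bias. The article fixes an unadjusted estimator while measuring the covariate that would sharpen it.

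The most secure figure is the variance reduction of about 46-70%, which needs the correlation range but no SD. It is larger if t1 is left out of the QALY. The shift of 0.0025-0.0083 QALY per one-SE imbalance depends on an assumed SD of 0.10-0.25. The article does not spell out the QALY formula, so the trapezium rule is also an assumption.

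For costs the gain is precision only, rests wholly on an unknown correlation, and applies only if costs are measured at t0. The primary efficacy conclusion on caregiver burden is untouched. The change is worth making before the data are analysed.

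**What to change.** Within each imputed and bootstrapped dataset, estimate incremental QALYs by regression on arm and baseline EQ-5D utility. Use the adjusted difference in the ICUR, the confidence intervals, the cost-utility plane and the acceptability curve, and report the raw difference as a sensitivity analysis. State which visits enter the QALY and by what formula.

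If the cost questionnaires are completed at t0, adjust incremental costs for baseline three-month costs in the same way.

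The cost is a sentence or two in the plan and a few lines of analysis code. The QALY change needs no new data and no additional participants. Specifying it in advance also avoids a decision on adjustment after the baseline comparison has been seen.

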Since caregiver burden could lead to a deterioration in quality of life, reductions in work productivity, and an increase in the use of healthcare resources [53], it is important to investigate the costs and effects related to caregiving, while investigating the effects of interventions [54]. In this study, medical costs, productivity costs, and costs of informal caregiving will be taken into account in the cost-utility analysis. It is expected that Oncokompas will improve QALYs at acceptable costs, compared to care as usual. This study will create knowledge on the impact of informal cancer care, which in its turn could serve as valuable information for policy makers to take into account while developing healthcare arrangements regarding the facilitation and support of informal caregiving.

This study will also contribute to the knowledge about the effectiveness of eHealth interventions used by partners of patients with incurable cancer. When Oncokompas is proven to be effective for partners, this may stimulate the implementation of the intervention as a health service for partners of cancer patients.

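### The friction cost method is applied to unpaid work, which it cannot value, and the plan does not say where the partner's informal care enters the societal total

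*Protocol article*

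**What the plan says.** The Economic outcomes section of the protocol article gives the operative cost rules. The societal total has four components.

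- Intervention costs and healthcare costs: "Total costs from a societal perspective will be calculated using intervention costs, costs of healthcare (i.e. costs of healthcare and medication".
- Family costs: "costs for patients and their families (e.g. travelling costs and help received from family and friends".
- Other-sector costs: "costs within other sectors (i.e. productivity losses from paid and unpaid work".

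Two valuation rules follow. For healthcare and family costs: "Costs of healthcare and costs for patients and their families will be calculated by multiplying resource use by integral costs prices". For the remaining category: "The friction cost method will be used to calculate the costs within other sectors". Multiple imputation is then promised for missing healthcare, family and other-sector costs and for EQ-5D utilities. The healthcare perspective uses intervention and healthcare costs only.

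Informal care appears in three other places. Table 3 (Outcome assessment) lists the cost measures for the cost-utility aim as "Medical costs Productivity costs Costs of Informal Care", with the iVICQ as the instrument for the last. The section on the three iMTA questionnaires says that an adapted iVICQ "will be used for the valuation of informal care by monetary and non-monetary methods". The Discussion says that "medical costs, productivity costs, and costs of informal caregiving will be taken into account in the cost-utility analysis".

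**The concern.** There are two problems, and the first is the firmer.

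First, the friction cost method values the output an employer loses between a worker's absence and that worker's replacement. It needs a job, a wage and a replacement period. Unpaid work has none of these. Applied as written, the rule leaves unpaid losses either at zero or at a price the document does not state.

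Second, the document says in two places that informal caregiving costs are part of the cost-utility analysis, but the section that defines the calculation never names them. Participants are partners who often provide care, so their caregiving time is an item a reader would look for in a societal total.

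The societal perspective differs from the healthcare perspective only by the family and other-sector components, and both problems lie there. Two analysts following this section in good faith could reach different societal totals, and the choice could be made after the data are seen.

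**Working it through.** The plan states no cost figure, caregiving hours or unit price, so there is no result of its own to reproduce. The check is a comparison of wording, followed by an illustration on assumed inputs.

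**1. Scope of the friction cost rule.** The other-sector category is defined by an i.e. list, which is closed: paid and unpaid work. The valuation sentence then takes the whole category without exception. The rule therefore covers unpaid work by its own terms.

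**2. Where informal care is named.**

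| Place | Partner's informal care or iVICQ named? |
|---|---|
| Table 3, cost-utility rows | Yes, as a separate measure |
| Section on the three questionnaires | Yes, with the iVICQ as its own instrument |
| Discussion | Yes, as part of the cost-utility analysis |
| Economic outcomes: societal total | No |
| Economic outcomes: valuation rules | No |
| Economic outcomes: imputation list | No |

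**3. Could family costs contain it?** That category is an e.g. list, so it is open, and help received from family and friends could be read as care the patient receives from the partner. The questionnaire section points the other way. It uses the same help-received wording for costs collected with the iMCQ and iPCQ, and then gives informal care to the iVICQ in a separate sentence. The document thus treats them as two items, but does not exclude the wider reading.

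**4. Valuation.** The iVICQ is to be valued by both monetary and non-monetary methods. Only a monetary result can be added to a cost total, and the Economic outcomes section does not say which one.

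**5. Illustration (inputs assumed, not from the document).** Take an arm difference of 1 to 5 caregiving hours a week, 13 weeks, and EUR 10 to 20 per hour.

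- Low: 1 × 13 × 10 = EUR 130 per participant.
- High: 5 × 13 × 20 = EUR 1,300 per participant.

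The horizon is three months, a quarter of a year, so QALY differences are small. An assumed utility difference of 0.05 held throughout gives 0.05 × 0.25 = 0.0125 QALY. On that assumption the ICUR would shift by 130 / 0.0125 = EUR 10,400 to 1,300 / 0.0125 = EUR 104,000 per QALY. This shows only that the item can matter. It says nothing about which arm would have the higher cost, or whether the arms differ at all.

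**The case against.** The strongest reply is that a journal article condenses. Three places say informal care is counted or valued, and only one section does not name it. The family-cost list is open, and a partner is family. The exact cost line and hourly price are details that the full protocol or an economic analysis plan may hold. The friction cost sentence may be shorthand, and the costing sources it cites cannot be consulted here.

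Much of this stands for informal care. A reader might infer that the plan leaves the partner's care out of the societal ICUR. The document does not support that: the e.g. list leaves room for it, and the Discussion states that it is included. What remains is that the section defining the calculation does not agree plainly with Table 3 and the Discussion, and that the questionnaire section separates help received from informal care.

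The reply is weaker for unpaid work. The category is closed by definition and the method is applied to all of it. That is a stated rule and not a missing detail, even if practice would depart from it.

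A reader might also infer that caregiving time is the largest societal cost, or that the intervention would shift it. Nothing in the document shows either. The intervention is described as focused on the partner's own self-care, and no aim of reducing caregiving hours is stated. Nor are the items that do separate the two perspectives wrong in general: travel, family costs and paid productivity losses are proper societal costs.

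**Conclusion.** The point holds in two parts of unequal strength. Applying the friction cost method to unpaid work is a stated rule that cannot give a valid value for that item. The treatment of informal care is an internal inconsistency: Table 3 and the Discussion count it, while the societal total, valuation rules and imputation list do not name it.

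The effect is confined to societal-perspective costs and the ICUR, cost-utility plane and acceptability curve built on them. The CSI+ analysis, the sample size, the QALYs and the healthcare-perspective result are untouched. Size and direction cannot be derived from the document, and the euro figures above rest wholly on assumed hours, prices and utility difference. The planned sensitivity analyses on the main cost factors do not settle the base case. It should be corrected before the economic analysis, but it does not threaten the trial's primary conclusion.

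**What to change.** In the Economic outcomes section:

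1. Restrict the friction cost method to productivity losses from paid work.
2. Value lost unpaid work by a stated hourly price. Replacement cost is one option; others are defensible if fixed in advance.
3. Name informal care given by the partner, measured with the iVICQ, as a component of the societal total, with one stated monetary valuation. Keep non-monetary results outside the total.
4. Add informal care to the imputation list.
5. State that each hour is counted once across informal care, lost unpaid work and help received, and define whose help the last item covers.
6. Make Table 3, the questionnaire section, the Economic outcomes section and the Discussion agree.

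The cost is wording and one cost line. The instruments are already planned, so no new data collection should be needed, provided that the adapted iVICQ records what the chosen valuation requires (for example, hours of care). That should be confirmed, since the adaptation is not described in the article.
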